#### Plans to promote participant retention and complete follow-up {18b}

N/A — participation by patient is only required while in ICU. Follow-up requires using healthcare records and information from primary care providers only. This is an intention-to-treat study design.

#### Data management {19}

All electronic information held will be kept on a password-protected, audited server maintained by the CRO, accessible only to authorised study personnel and compliant with ICH GCP.

All study material, including case report forms and the study database, will be stored for a minimum period of 15 years after the conclusion of the study or as per national/European legislation.

Source documents are the documents or media where the patients’ data are first recorded, and from which the data participants’ entered into the eCRF data is obtained. These include, but are not limited to, data gathered from health records at the treating institution, medical records from other institutions where applicable.

Sources of data will be identified and pre-specified on a study-specific source data agreement relevant to the study site. The source data agreement will be verified by the principal investigator with a copy of the agreement to be filed within the site file.

The site investigator(s) will facilitate the permit of study-related monitoring, audit, research ethics committee approval review and regulatory inspection by the relevant national authority/international, providing direct access to source documents where possible.

Data collected will be pseudo-anonymised; on all study-specific documents other than the signed consent, the subject will be referred to by the study subject identification number/code.

Subject participation and subject progress should also be recorded in the subject medical records to ensure relevant healthcare providers have knowledge of the subject’s participation in the study.

Data from medical records will be entered by authorised and delegated site personnel into the electronic case report form. The data will be verifiable against original records and source notes by the Monitor during monitoring visits. Data reported on the eCRF that are derived from source documents must be consistent with the source documents or the discrepancies must be explained.

eCRF completion instructions will be provided and any questions about recording specific information on the eCRF should be directed to the investigator. Each participating centre will maintain a subject identification log of enrolled patients that includes patient identifiers. Patient identifiers are not transferred to the study coordinating centre.

#### Confidentiality {27}

Only authorised study staff will be permitted access to the password-protected study database where study-specific data will be stored. Paper documents will be stored in a locked site with restricted access. On all trial-specific documents, other than the signed consent form and the enrolment log, the participant will be referred to by the unique participant code, not by name. Patient identifiable data will not leave the site, as per the Data Protection Act. Access will be granted to authorised representatives from the sponsor and the regulatory authorities to permit trial-related monitoring, audits and reports.

Subject confidentiality will be maintained at all times and no documents containing the subject’s name or other identifying information will be collected by the sponsor on the study database. It may be necessary for the sponsor’s representatives, the ethics committee and regulatory authority representatives to have direct access to the subject’s medical records.

#### Plans for collection, laboratory evaluation and storage of biological specimens for genetic or molecular analysis in this trial/future use {33}

Blood samples collected for analysis of interleukin and tissue necrosis factor levels will be stored during the study in the recruiting hospital in temperature monitored laboratory refrigerators. Following completion of recruitment and sample collection, samples will be transferred by a specialist biochemical sample transport company to the primary centre (NUIG/UHG) for processing. This approach has been taken as some of the inflammatory cytokine analyses are not standard assays in the laboratory of the recruiting centres. Only the described analyses will be carried out on these samples, with unused portions of these samples destroyed according to standard laboratory SOPs.

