**Methods:**

This is a multi-centre, phase 1b/IIa, randomised, parallel-group, open-label study. The study will randomise 40 SARs-CoV-2-positive patients receiving advanced respiratory support in a critical care area. Randomisation will be via 1:1 allocation to usual care plus nebulised unfractionated heparin 6 hourly to day 10 while receiving advanced respiratory support or usual care only. The study aims to evaluate whether unfractionated heparin will decrease the procoagulant response associated with ARDS up to day 10. The study will also assess safety and tolerability of nebulised heparin as defined by number of severe adverse events; oxygen index and respiratory oxygenation index of intubated and unintubated, respectively; ventilatory ratio; and plasma concentration of interleukin (IL)-1β, IL6, IL-8, IL-10 and soluble tumour necrosis factor receptor 1, C-reactive protein, procalcitonin, ferritin, fibrinogen and lactate dehydrogenase as well as the ratios of IL-1β/IL-10 and IL-6/IL-10. These parameters will be assessed on days 1, 3, 5 and 10; time to separation from advanced respiratory support, time to discharge from the intensive care unit and number tracheostomised to day 28; and survival to days 28 and 60 and to hospital discharge, censored at day 60. Some clinical outcome data from our study will be included in the international meta-trials, CHARTER and INHALE-HEP.

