## Trial status

The CHARTER-Ireland trial commenced December 23, 2020, at University Hospital Galway, Ireland. Recruitment is proceeding using protocol version 7, 22 February 2021. We expect to complete recruitment in Spring 2022.

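### As written, blood for the cytokine outcomes is refrigerated until recruitment ends (about 14 to 18 months for the earliest patients), so the cytokine AUCs and ratios may be attenuated and noisier unless stability is shown

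*Protocol article*

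**What the plan says.** Section {33} of the protocol article sets the storage rule for one group of samples, described as "Blood samples collected for analysis of interleukin and tissue necrosis factor levels". These "will be stored during the study in the recruiting hospital in temperature monitored laboratory refrigerators". The end of storage is also fixed: "Following completion of recruitment and sample collection, samples will be transferred by a specialist biochemical sample transport company to the primary centre", where they are processed. The reason given is that "some of the inflammatory cytokine analyses are not standard assays in the laboratory of the recruiting centres".

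The Trial status section supplies the dates: "The CHARTER-Ireland trial commenced December 23, 2020" and "We expect to complete recruitment in Spring 2022".

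Outcomes {12} makes the AUCs of these markers over days 1, 3, 5 and 10, and the IL-1β/IL-10 and IL-6/IL-10 ratios, secondary efficacy outcomes. The Methods part of the abstract names the measured quantity as "plasma concentration of interleukin (IL)-1β, IL6, IL-8, IL-10 and soluble tumour necrosis factor receptor 1".

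**The concern.** The article does more than leave storage to a laboratory manual. It states the equipment, the duration and the event that ends storage. Followed literally, the first patients' samples sit in a refrigerator for well over a year and the last patients' samples for a short time. The stated reason justifies assaying in one batch. It does not explain why samples are refrigerated in the meantime. The section also puts processing after transfer and mentions only blood, although the abstract promises plasma concentrations.

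If the analytes decline under these conditions, three things follow:

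- Absolute AUC differences shrink in proportion to the loss, and low values may drop below the assay's detection limit.
- Loss depends on enrolment date, so calendar time adds variance between patients.
- The two ratios shift if numerator and denominator decay at different rates.

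A null cytokine result could then not be told apart from sample loss. Section {33} also has unused portions destroyed, so no material is kept for a later check.

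**Working it through.** The article states no storage duration or loss rate, so there is no figure of its own to reproduce.

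**1. Longest hold.** Inputs from Trial status: start on 23 December 2020, recruitment expected to end in spring 2022 with no month given. Days from the start, divided by 30.44:

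| Assumed end of recruitment | Days | Months |
|---|---|---|
| 1 March 2022 | 433 | 14.2 |
| 20 March 2022 | 452 | 14.9 |
| 30 April 2022 | 493 | 16.2 |
| 31 May 2022 | 524 | 17.2 |
| 21 June 2022 | 545 | 17.9 |

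The maximum is therefore about 14 to 18 months, assuming that a first sample was drawn close to the start date and that transfer follows soon after recruitment closes. It applies only to the earliest patients.

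**2. Analyte remaining.** Assumption, not from the documents: first-order loss at rate r per month, with r between 1% and 10%. The fraction left after t months is (1 − r)^t.

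- r = 1%: 0.99^15 = 0.860 and 0.99^17 = 0.843, so 84–86% is left.
- r = 10%: 0.90^15 = 0.206 and 0.90^17 = 0.167, so 17–21% is left.

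**3. Added variance.** Assumption: holding times are spread evenly over 0 to 16 months. Their SD is 16/√12 = 4.62 months. The SD added on the log scale is −ln(1 − r) × 4.62.

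- r = 1%: 0.01005 × 4.62 = 0.05.
- r = 10%: 0.1054 × 4.62 = 0.49.

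For scale, assume a true between-patient log SD of 1.0, which is also not in the documents. At 10% per month the variance rises to 1 + 0.49² = 1.24. That is like losing 1 − 1/1.24 = 19% of the sample, about 8 of 40 patients. At 1% per month the rise is 0.05² = 0.0025, which is negligible.

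**4. Ratios.** After t months a ratio is multiplied by [(1 − r_num)/(1 − r_den)]^t. For IL-1β/IL-10 at t = 15:

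- equal loss rates: factor 1, no distortion;
- IL-1β 10%, IL-10 1%: (0.90/0.99)^15 = 0.24;
- the rates swapped: 1/0.24, about 4.2.

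Neither the direction nor the size is known.

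**5. Balance between arms.** Sequence generation {16a} and Concealment mechanism {16b} give 1:1 allocation in variable blocks at site level, so holding time should be similar in the two arms. One patient's samples differ in age by only about 10 days, so that patient's course over time is largely preserved up to a common scale factor. Under the first-order model that factor is expected to cancel from a between-arm comparison of logged values. The added variance does not cancel.

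**The case against.** The strongest objection is that the article is a summary. Under Plans to give access {31c} the full protocol is available on application. Temperature set-points, separation and aliquoting are commonly left to such documents, and refrigerator without a temperature may be loose wording for monitored frozen storage. This stands in part: the missing detail is no fault in itself, and actual practice may be sound. It does not clear the text, because the equipment and duration are stated. If samples are frozen, the stated rule is wrong and should be corrected.

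A reader might infer that the cytokine AUCs and ratios will not reflect levels in the patient. The documents do not support that. They give no storage temperature and no stability data, so the harm is conditional. The 0.49 SD and the 24% ratio are the unfavourable ends of an assumed range.

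A reader might also infer bias towards one arm. Blocking within site makes that unlikely.

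Nor does the problem remove all of the trial's evidence on inflammation. The storage rule covers only the interleukin and TNF-related samples. CRP, procalcitonin, ferritin, fibrinogen and LDH lie outside it, as do both co-primary outcomes and the d-dimer basis of the sample size.

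**Conclusion.** The point holds in conditional form. As written, the samples for five cytokine markers are refrigerated for up to about 14 to 18 months, with a hold that varies widely by enrolment date. Unless stability under those conditions is documented, the AUCs and the two ratios may be attenuated and noisier, and the ratios distorted if decay rates differ. The expected consequence is lost precision and an uninterpretable null result.

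The size cannot be fixed from the documents. It runs from minor to serious across the assumed loss rates, which are illustrations and not estimates. Because only secondary outcomes are exposed and the wording may misdescribe practice, this should be put right but is not a critical defect of the trial.

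**What to change.** Change section {33} to specify prompt plasma separation after each draw, aliquoting, monitored frozen storage at the site, and frozen shipment for the batch assay. If samples are already handled this way, replace the reference to refrigerators and state the actual temperature, the processing before storage and the maximum holding time.

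For samples already refrigerated, record the days held for each one. Limit the main cytokine analysis to samples within a documented stability limit, or adjust for storage time, which is not among the example covariates in Statistical methods {20a}. Report the analysis of all samples as a sensitivity analysis. Choose the approach before the assay results are seen by arm.

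The cost is revised wording, frozen shipment and freezer space for about 160 sample sets (40 patients × 4 sampling days). Some early samples may drop out of these secondary outcomes.

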### Statistical methods

#### Statistical methods for primary and secondary outcomes {20a}

Demographic and baseline characteristics of the study population will be summarised using appropriate graphical and numerical summaries for each treatment group and by site. The primary analysis approach will be an intention-to-treat analysis, with a per-protocol analysis also being carried out. The per-protocol analysis will include any patient who received any dose of the study drug in the treatment group and any patient who underwent data collection for at least one time point in the standard care group. A safety analysis set will be included including all recruited patients. For effectiveness analysis, we will use the 2-sample *t*-tests (or suitable non-parametric test depending on data distribution) for the between-group difference in d-dimer levels and generalised linear (or non-linear as appropriate) mixed effects models for the analysis of longitudinal data, using appropriate link functions depending on the type of outcome variable. This analysis will be used to compare the treatment effect, while adjusting for patient characteristics (e.g. Horowitz index of lung function (P/F ratio), Sequential Organ Failure Assessment (SOFA) score, body mass index (BMI), sex and age) as appropriate for all primary and secondary efficacy outcomes. A Cox proportional hazards model will be used to model time to event responses. Generalised linear models will be used for the analysis of safety outcomes. Primary and secondary outcome data will be suitable for meta-analysis to further assess clinically relevant outcomes. Interval estimates (95% confidence intervals) for the treatment effect will be reported accordingly.

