#### Intervention description {11a}

Participants assigned to ‘nebulised heparin’ will receive 5ml heparin sodium 5000 I.U./ml (25,000 I.U. in 5 ml), manufactured by Pinewood laboratories, Ballymacarbry, Clonmel, Co. Tipperary. This will be administered via the Aerogen solo nebuliser every 6 h from enrolment to day 10, in addition to the standard care required as determined by the treating team. Participants assigned to ‘standard care’ will receive the standard care required as determined by the treating team and will not be treated with nebulised heparin.

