#### Methods for additional analyses (e.g. subgroup analyses) {20b}

Results will be presented as per-protocol and intention-to-treat analysis groups. Results will also be presented for ventilated at enrollment and non-ventilated at enrollment subgroups, although due to the sample size the numbers in each group will be small.

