#### Methods in analysis to handle protocol non-adherence and any statistical methods to handle missing data {20c}

All participants who are enrolled will be included in the analysis. Any participants who withdraw and wish to have their data withdrawn will not be included. Analysis will be carried out using the intention-to-treat principle where patient’s data will be analysed as members of the group they were randomised to, irrespective of their compliance with the treatment as specified in the protocol. A separate per-protocol analysis will be carried out including all patients who complied with the protocol in terms of exposure to planed treatment, availability of measurements and absence of major protocol deviations. Any deviation(s) from the original statistical plan will be described and justified in the final report. [An analysis of all missing data will be carried out to identify the likely missing data mechanism (e.g. missing completely at random, missing at random, and missing not at random) and to investigate the reasons for missingness as a useful outcome for the corresponding subsequent definitive trial.] Multiple imputation using chain equations will be used to handle missing data (due to outcome values missing in some visits for some of the participants) in the primary and secondary outcome analysis.

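### The one per-protocol set has two conflicting definitions, and one of them is a treated-type set with different entry rules in each arm

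*Protocol article*

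**What the plan says.** All references are to the protocol article.

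- **Role and number of sets.** Intention-to-treat is primary: "The primary analysis approach will be an intention-to-treat analysis, with a per-protocol analysis also being carried out" (section {20a}). The additional analyses section {20b} speaks of one per-protocol group: "Results will be presented as per-protocol and intention-to-treat analysis groups".
- **First definition, section {20a}.** For the heparin arm: "The per-protocol analysis will include any patient who received any dose of the study drug in the treatment group". For the control arm: "any patient who underwent data collection for at least one time point in the standard care group".
- **Second definition, section {20c}.** The per-protocol analysis takes in "all patients who complied with the protocol in terms of exposure to planed treatment, availability of measurements and absence of major protocol deviations". This is not split by arm.
- **Planned exposure.** The intervention description {11a} has heparin "administered via the Aerogen solo nebuliser every 6 h from enrolment to day 10". The trial design section {8} limits this to time on advanced respiratory support, and Table 2 lists the circumstances in which doses are to be withheld.

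**The concern.** The same label is attached to two different membership rules, and nothing in the article ranks them or says that one replaces the other.

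The {20a} rule does not describe a per-protocol set. It asks nothing about adherence beyond the first dose and nothing about deviations. It also admits the two arms on different grounds: drug exposure in one, data collection in the other. A randomised heparin patient who was never dosed but has data is dropped, and no matching rule removes a control.

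What is at stake is the meaning of the supporting result. Readers will take a per-protocol estimate as showing what happens when the allocated treatment is followed. Under {20a} it would not show that. With both rules in print, two analysts could each follow the published plan and report different sets.

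**Working it through.** The plan states no figure for this point, so there is none to reproduce. The check is a comparison of the two rules, with a little arithmetic for scale.

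**Conditions compared**

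| Condition | {20a}, heparin | {20a}, control | {20c}, both arms |
|---|---|---|---|
| Exposure | at least one dose | none stated | complied with planned treatment |
| Measurements | none stated | at least one time point | available (extent not stated) |
| Major deviations | none stated | none stated | must be absent |

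**Patients on whom the rules disagree**

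1. A heparin patient takes one or more doses, then stops in breach of the protocol. In under {20a}; out under {20c}.
2. A heparin patient has been dosed but has no available measurements. In under {20a}; out under {20c}.
3. A control has data at one time point and a major deviation, for instance receiving nebulised heparin, which {11a} says controls will not be given. In under {20a}; out under {20c}.

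The sets coincide only if no such patients occur.

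**Is a second per-protocol set intended?** Section {20c} says: "A separate per-protocol analysis will be carried out including all patients who complied with the protocol in terms of exposure to planed treatment". The sentence just before it describes the intention-to-treat analysis, so the natural reading is that this analysis is separate from that one. Section {20b} also names a single per-protocol group.

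**Scale**

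- Planned doses if none is ever withheld: one every 6 h is 24/6 = 4 per day, and 4 × 10 days = about 40. This is a ceiling, given Table 2 and the restriction to time on advanced respiratory support.
- The least exposure that qualifies under {20a}: 1/40 = 2.5% of that ceiling.
- Weight of one patient, with 20 per arm from the sample size section {14}: 1/20 = 5% of an arm. This is a headcount, not an effect on the estimate.
- Change in the per-protocol estimate: not computable, because the article gives no adherence or deviation rate.

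**The case against.** The strongest reply is that little depends on this. Intention-to-treat is explicitly primary, the trial is a 40-patient phase 1b/2a study, and no success criterion rests on the per-protocol result. The analysing statistician is blinded to allocation {17a}, and {20c} requires deviations from the statistical plan to be described and justified. These points stand and limit the severity. They do not settle which rule applies: with two written definitions, following either one is not a deviation.

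A second reply is that a fuller analysis plan may resolve the matter. It may, but the published article, whose title presents it as both protocol and statistical analysis plan, would still state two rules. The point concerns a contradiction in the text, not absent detail.

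Three stronger readings are tempting, and the article does not support them.

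- **That anyone with 1 of 40 doses is excluded under {20c}.** That section sets no dose threshold. A patient whose later doses were withheld under Table 2, for example after coming off advanced respiratory support, followed the protocol. Only stopping in breach of it puts the two rules in conflict.
- **That both rules select the arms differently.** Only {20a} is arm-specific. Section {20c} applies the same criteria to both arms. An exposure condition may remove more heparin patients in practice, but that is true of any per-protocol set.
- **That {20c} removes early deaths and ICU leavers.** It may. Daily data are gathered only in the ICU {18a}, so biomarker series can be cut short. But the section does not say how many measurements are needed, and it plans multiple imputation for outcomes missing at some visits.

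**Conclusion.** The point holds as a contradiction within the article. One named analysis set has two membership rules that disagree for identifiable patients, and the {20a} rule is a treated-type set with arm-specific entry and no adherence or deviation condition. A result reported as per-protocol under {20a} would be mislabelled.

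The consequence is confined to the supporting analysis. A reader might infer that the trial's main conclusion is at risk, or that the choice of set could be made freely once results are known. The first does not follow, because the primary analysis is intention-to-treat. The second goes too far given the blinded statistician and the duty to justify deviations, although the choice between the rules remains open.

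The conclusion assumes that only one per-protocol set is intended, as {20b} indicates, and that at least one patient will be non-adherent outside Table 2, have a major deviation, or be dosed without available measurements. This should be corrected before analysis. It is no reason to doubt the design.

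**What to change.** 1. Keep one per-protocol definition, based on {20c}: adherence to the allocated treatment and no major protocol deviation. Apply the same eligibility and deviation criteria to both arms.
2. State what counts as adherent in the heparin arm, with doses withheld under Table 2 counted as compliant.
3. Rename the {20a} set as a treated set, or delete it. If it is kept, do not present it as per-protocol.
4. Do not use availability of measurements as an exclusion condition. It may select patients on what happened after randomisation, and {20c} already plans multiple imputation for missing outcome values.
5. Fix the list of exclusions, with reasons, before the statistician is unblinded.

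The cost is small: a change of wording in two sections and one real decision, namely what counts as adherent. No change to data collection, sample size or the primary analysis is needed.

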#### Sample size {14}

This is a phase 1b/2a study aiming to evaluate the effect of nebulised unfractionated heparin on procoagulant markers and the safety of nebulised heparin in patients receiving advanced respiratory support for COVID-19 lung disease. This has not been studied previously, and as such, data does not exist to power the study accurately to assess clinical outcomes. We have chosen to base our power analysis on some of our own in house data for d-dimer levels in COVID patients who required ICU care (12 patients) and those who did not (26 patients) (unpublished data from very early in the pandemic).

Based on an estimation that nebulised heparin may reduce the d-dimer levels in ICU patients (mean = 944.8ng/ml [SD = 485.3]) to those experienced in ward patients (mean = 436.5ng/ml [SD = 604.0]), with an alpha level of 0.05 and a power of 90% to detect a type II error, 19 patients per group would be required. Increasing the number by 1 per group to allow for potential dropout gives a sample size of 20 patients per arm of the study, with a total of 40 patients to be enrolled. The safety profile of administering nebulised heparin to invasively ventilated patients with COVID-19 will be a co-primary outcome. The study is not powered for analysis of the co-primary endpoint of serious adverse events due to insufficient pre-existing data in this population. Power analysis is based only on the outcome of d-dimer as described above.

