#### Concealment mechanism {16b}

Blocks of variable size and a random seed will be used to ensure allocation concealment cannot be violated by deciphering the sequence near the end of each block. To further protect from deciphering, block size will not be revealed to site investigators. Site-level randomisation will be used. At randomisation, each participant is assigned to nebulised heparin or standard care. There is a one-to-one allocation ratio.

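### The d-dimer co-primary has two competing analyses with neither named as decisive, and the listed covariates leave out baseline d-dimer and site

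*Protocol article*

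**What the plan says.** All references are to the protocol article.

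- **Simple test.** Section {20a} assigns d-dimer a two-sample t-test, with an alternative: "or suitable non-parametric test depending on data distribution) for the between-group difference in d-dimer levels". The alternative test is not named, and no rule for choosing it is given.
- **Model.** The same sentence adds generalised linear or non-linear mixed models for longitudinal data. The next sentence plans covariate adjustment in the comparison of the arms, and its list of examples opens like this: "adjusting for patient characteristics (e.g. Horowitz index of lung function (P/F ratio), Sequential Organ Failure Assessment (SOFA) score, body mass index (BMI". Age and sex complete the list. The adjustment is meant to reach every efficacy outcome, whether primary or secondary, where suitable. D-dimer, measured repeatedly, falls under this too.
- **Site.** The concealment section {16b} states: "Site-level randomisation will be used". It goes on to say that each participant is assigned to an arm, so this means individual allocation within site. The study setting section lists three units.
- **Baseline.** Table 1 requires d-dimer above 200 ng/ml at entry. The outcomes section {12} defines the AUC on days 1, 3, 5 and 10. The participant timeline {13} has the blood samples on days 0, 3, 5 and 10.
- **Scale.** No analysis scale is stated. Only the sample size section {14} works in ng/ml: "ICU patients (mean = 944.8ng/ml [SD = 485.3"]) against "ward patients (mean = 436.5ng/ml [SD = 604.0"]).

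**The concern.** A t-test, a rank test and an adjusted mixed model answer different questions and can disagree in 40 patients. The t-test and the rank test do not even share an effect measure: one compares means, the other compares orderings. Section {20a} promises 95% confidence intervals for the treatment effect, and a rank test does not directly supply one for a mean difference. If the analyses disagree, the article gives no basis for saying which one is the trial's result.

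The covariates matter for a separate reason. A continuous outcome's own baseline is usually among its best predictors, and chance imbalance in it passes into an AUC that contains the first sample. Site is part of the allocation scheme, so an analysis that leaves it out does not reflect how patients were randomised. Five other characteristics are named as examples and these two are not.

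**Working it through.** **Inputs** (sample size section {14}): means 944.8 and 436.5, so the difference is 508.3 ng/ml; SDs 485.3 and 604.0; alpha 0.05 with sidedness not stated; 20 per arm.

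Common SD = √[(485.3² + 604.0²)/2] = √300,166 = 547.9. Standardised effect = 508.3/547.9 = 0.928.

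**1. The plan's own figure.** The article states: "with an alpha level of 0.05 and a power of 90% to detect a type II error, 19 patients per group would be required". With n per arm = 2[(z_α + z_β) × SD/508.3]²:

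- two-sided, both SDs: 24.4, so 25;
- two-sided, ICU SD only: 19.2, so 20;
- one-sided, both SDs: 19.9, so 20.

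The stated 19 is therefore approached only with the ICU SD alone or a one-sided test. That is a separate point. It is noted here because it sets the unadjusted starting power.

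**2. Unadjusted t-test, 20 per arm, two-sided 0.05.** Noncentrality = 508.3/(547.9 × √(2/20)) = 2.934; 38 df; critical value 2.024; power 81.6%.

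**3. Covariate adjustment.** Let r be the correlation between baseline and outcome within arms (an assumption, shown as a range) and k the number of covariate parameters. The residual SD is 547.9 × √(1 − r²), df = 38 − k, and the variance of the treatment contrast is inflated for expected chance imbalance by 1 + k/(37 − k). That factor is 1.028 for baseline alone (k = 1) and 1.088 for baseline plus three sites (k = 3).

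Example, r = 0.5 and k = 1: noncentrality = 508.3/(547.9 × 0.866 × 0.3162 × √1.028) = 3.34; 37 df; power 90.2%.

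| r | Unadjusted | Baseline only | Baseline + uninformative site |
|---|---|---|---|
| 0 | 81.6% | 80.5% | 78.1% |
| 0.3 | 81.6% | 84.0% | 81.8% |
| 0.5 | 81.6% | 90.2% | 88.4% |
| 0.7 | 81.6% | 97.6% | 96.9% |

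With both terms and a site effect of nil, break-even is at about r = 0.3. The largest loss is 81.6 − 78.1 = 3.5 points. The site column is somewhat pessimistic, since blocking within site limits imbalance between arms.

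**4. Scale.** The ward SD exceeds the ward mean (604.0/436.5 = 1.38). A normal curve with those values would put 23.5% of readings below zero. The ICU figures give a ratio of 0.51 and 2.6% below zero. This suggests skewness in single readings. It does not show how the AUC is distributed.

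**5. The distribution-based choice of test.** Simulation with lognormal data at the plan's means and SDs (an assumption), 20 per arm: power is about 82 to 83% for the t-test on raw values, 99% on logs and 99% for the rank test. A switch triggered by a Shapiro-Wilk test in either arm moves to the rank test in about 97% of trials and also gives about 99%. Under the null at 19 per arm, the same kind of switch had type I error of 4.6 to 4.7%. Taking the smaller of the two p-values would give 5.6 to 6.4%.

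**The case against.** The strongest reply is that the plan already adjusts. Section {20a} extends adjustment to all primary outcomes, and its covariate list is illustrative, so baseline d-dimer and site are unnamed and not excluded. An article may leave the final covariate set to a fuller document. This is correct as far as it goes: a reader might infer that the whole primary analysis is unadjusted, and the text does not support that. It does not answer the main point. The article's title says it includes the statistical analysis plan, and it fixes two analyses for one co-primary without ranking them.

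Three further inferences should also be resisted.

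- **That a raw-scale t-test forfeits power, from about 99% to 83%.** The raw scale is inferred only from the sample size section, and the plan's own fallback to a rank test recovers almost all of that difference under the same lognormal assumption.
- **That choosing the test on the distribution inflates type I error.** Section {17a} blinds the analysing statistician to allocation, and the simulated switch stayed below 5%. The cost is a changing effect measure.
- **That adjustment restores 90% power.** It does so at r = 0.5 with baseline alone, but not once an uninformative site term is charged (88.4%), and r is unknown.

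Adding invasive ventilation as a further term would cost a little more: about 81%, 87% and 97% at r = 0.3, 0.5 and 0.7. The article plans ventilation only as a subgroup display ("Results will also be presented for ventilated at enrollment and non-ventilated at enrollment subgroups"), and the point does not depend on including it.

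**Conclusion.** The point holds in this form: the decisive analysis of the d-dimer co-primary is not designated, and the two covariates with the clearest claim to inclusion are not among those named. It should be corrected before analysis, but it does not invalidate the design.

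Against 81.6% unadjusted, adjusting for baseline and an uninformative site ranges from a loss of about 3.5 points at r = 0 to a gain of about 15 points at r = 0.7 (96.9 − 81.6 = 15.3). This rests on a two-sided 0.05 test, all 20 patients per arm analysed, the plan's single-reading means and SDs standing in for the AUC, a common SD of 547.9, and an assumed r. The ambiguity over which analysis decides rests on none of these. It is plain from the text.

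**What to change.** Before the data are analysed:

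1. Designate one primary d-dimer model, an ANCOVA of the AUC or an equivalent repeated-measures model, with arm, pre-dose d-dimer and site as terms.
2. Fix the scale in advance. The log scale is a sensible choice given the skewness the ward figures suggest, with the effect reported as a ratio of geometric means and its 95% confidence interval.
3. Reconcile day 1 in section {12} with day 0 in section {13}, and define which sample is the pre-dose value. Section {11a} starts the intervention at enrolment, so a day 1 sample could follow the first dose, and adjusting for it could remove part of the treatment effect. State whether the pre-dose value also counts in the AUC.
4. Label the t-test, the rank test and the models with P/F ratio, SOFA, BMI, sex and age as supportive.

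The cost is wording. Entry d-dimer and site are already known for every patient. The statistical price is one to three degrees of freedom, and on the log scale the result is read as a ratio instead of a difference in ng/ml.
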